NBO therapy involves delivering oxygen at atmospheric pressure but at a higher fraction than the ~21% found in ambient air. In contrast, hyperbaric oxygen therapy (HBOT) uses both an elevated oxygen concentration and increased atmospheric pressure (typically ≥1.4 ATA), necessitating specialized pressurized chambers [14]. While HBOT has been studied extensively for conditions such as radiation-induced tissue damage, diabetic foot ulcers, and wound healing, NBO offers a more accessible alternative with fewer risks (e.g., lower incidence of barotrauma, reduced logistical constraints) and may be easier to implement in a variety of clinical settings [15]. Mechanistically, NBO may support erythropoiesis, reduce oxidative stress, and modulate immune function through several pathways. First, by delivering a higher oxygen fraction at normobaric pressure, NBO can alleviate tissue hypoxia—including in the kidneys—which may help preserve or enhance endogenous erythropoietin (EPO) production [16]. Second, the improved oxygenation can potentially reduce the generation of reactive oxygen species (ROS) by optimizing mitochondrial function, thereby attenuating oxidative stress and cellular damage [17]. Third, improved oxygen availability in tissues has been hypothesized to counteract tumor hypoxia, which can otherwise promote immunosuppressive mechanisms (e.g., upregulation of immune checkpoint molecules and recruitment of myeloid-derived suppressor cells) [18,19]. Consequently, NBO could restore or enhance immune cell functionality, potentially improving the anti-tumor immune response in cancer patients [20,21,22].

Recent research has explored the potential benefits of NBO in various medical conditions, including its role in supporting erythropoiesis, reducing oxidative stress, modulating immune function, and improving stress, emotional well-being, and cognitive functions in patients [23].

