### 2.5. Randomization and Blinding

Participants will be randomized in a 1:1 ratio to the active NBO (study) or placebo NBO (control) group using a stratified randomization method. Stratification factors include CRC stage (II vs. III vs. IV) and baseline hemoglobin levels (<12 g/dL vs. ≥12 g/dL), as these variables can significantly influence treatment outcomes and the incidence of anemia. A computer-generated allocation sequence will be used within each stratum to ensure an even distribution of these characteristics across the two study arms. Only the NBO operators (who are not involved in data collection or analysis) will have access to the allocation list to administer the assigned intervention. All other study personnel and participants will remain blinded to group assignments.

Patients and clinical staff (excluding NBO operators who administer the therapy) will be blinded to the treatment allocations. Placebo NBO sessions mimic active NBO conditions without therapeutic oxygen adjustments. Both patients and clinical staff involved in patient care and data collection will be blinded to the treatment allocations. NBO operators who administer the therapy will not be blinded in order to ensure the correct delivery of the intervention. They will be trained to maintain confidentiality and avoid any disclosures that could compromise blinding. Both active NBO and placebo NBO sessions will be conducted in chambers that are identical in appearance and setup. This includes similar equipment, procedures, and environmental conditions in order to prevent patients and blinded staff from discerning group assignments.

Unblinding will occur after the database is locked and completion of statistical analysis. Immediate unblinding is permissible in medical emergencies where treatment knowledge is essential for patient care. Unblinding may occur immediately if a serious adverse event or medical emergency arises where knowledge of the treatment allocation is essential for the patient’s safe and effective management. The decision to unblind in an emergency will be made by the principal investigator or a designated medical officer.

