### 2.6. Intervention Planned

The intervention will involve NBO as a supportive treatment for CRC patients undergoing chemotherapy. The NBO protocol consists of regular sessions in a normobaric chamber where patients are exposed to controlled oxygen levels aimed at reducing oxidative stress, supporting erythropoiesis, and modulating immune function. Patients in the CRC group will undergo ten NBO sessions across five weeks, with two sessions weekly.

In our study, both the active NBO and placebo NBO groups will undergo sessions in the same normobaric chamber to ensure a consistent experience. For the active NBO group, the chamber will deliver an elevated oxygen concentration (32–40%), while for the placebo group, the oxygen level will be set to approximately 21% (room air). All other environmental parameters—such as chamber pressure, duration of sessions, and ambient conditions—will be identical between the two groups. To maintain the double-blind design, only the NBO operators, who will not be involved in data collection or analysis, will be aware of the specific oxygen settings. Visual indicators of oxygen concentration will be concealed, and the procedure will be standardized so that participants and blinded clinical staff cannot discern which treatment is being administered.

Prior to each NBO session, baseline oxygen saturation (SpO_2_) will be measured using standard pulse oximetry to account for inter-individual variations in oxygenation. If a participant exhibits a significant deviation from their established baseline or displays any clinical signs of respiratory compromise, an arterial blood gas (ABG) analysis will be performed to obtain a more precise measure of oxygenation and guide any necessary adjustments.

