#### 2.6.1. Active NBO (Study Group)

Patients will be exposed to NBO conditions in Study Group 1 (aNBO), including oxygen levels of 32–40% (compared with about 21% in the atmosphere), pressure maintained at 1500 hPa (compared with about 1000 hPa outside), carbon dioxide levels between 0.7 and 1.9% (compared with 0.03% in the atmosphere), and hydrogen levels between 0.5 and 1% (which is 10,000 to 20,000 times higher than in the atmosphere). The exposure time in the NBO chamber will be the standard 2 h with an additional 20 min for preparation and adaptation and 10 min for finalization and the decompression period.

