#### 2.6.2. Placebo NBO (Control Group)

Patients will be exposed to atmospheric conditions in the same NBO chamber (without normobaric conditions to provide a sham-placebo intervention) in Control Group 2 (pNBO), including oxygen levels at about 21%, pressure maintained at about 1000 hPa, carbon dioxide levels at about 0.03%, and hydrogen levels at about 0.00005% (0.5 parts per million, like in the atmosphere). The primary comparator in this study is the placebo NBO group (n = 127) for CRC patients, which serves to differentiate the specific effects of active NBO from the natural course of treatment without enhanced oxygen exposure.

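### Section 2.6 says the arms differ only in oxygen, but Sections 2.6.1 and 2.6.2 also give them different pressure, CO2 and hydrogen

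*Protocol article*

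**What the plan says.** The protocol article describes the contrast between the arms in two ways.

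**Matched except for oxygen.** Section 2.6 gives 32–40% oxygen in the active arm and about 21% in the placebo arm, then states: "All other environmental parameters—such as chamber pressure, duration of sessions, and ambient conditions—will be identical between the two groups". Section 2.5 describes the sham in the same sense: "Placebo NBO sessions mimic active NBO conditions without therapeutic oxygen adjustments". It also offers the match as a protection for the blind: "This includes similar equipment, procedures, and environmental conditions in order to prevent patients and blinded staff from discerning group assignments".

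**Different on four parameters.** Besides the oxygen level, Section 2.6.1 fixes two further settings for the active arm: "pressure maintained at 1500 hPa (compared with about 1000 hPa outside), carbon dioxide levels between 0.7 and 1.9% (compared with 0.03% in the atmosphere"). A third gas is also raised far above its background level, as the same section goes on to specify: "hydrogen levels between 0.5 and 1% (which is 10,000 to 20,000 times higher than in the atmosphere"). Its session timetable ends with "10 min for finalization and the decompression period". Section 2.6.2 puts the sham at about 21% oxygen, with "pressure maintained at about 1000 hPa, carbon dioxide levels at about 0.03%, and hydrogen levels at about 0.00005" per cent, and says outright that the sham is run at atmospheric conditions.

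No sentence reconciles the two descriptions or says which prevails.

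**The concern.** The sham determines what a randomised difference means. If it matches the active arm in everything but oxygen, a difference in outcome can be put down to raised oxygen concentration. If pressure, CO2 and hydrogen also change, the trial compares a package with room air.

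The scientific case is about oxygen. Section 1 argues from an effect obtained "by delivering a higher oxygen fraction at normobaric pressure", and Sections 4 and 5 argue from improved oxygen availability. Section 2.6.2 says the comparator represents treatment without enhanced oxygen exposure. CO2 and hydrogen have no place in the rationale in Section 1, Section 4 or Section 5.

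Two things are at stake:

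- **Delivery.** Operators cannot run the chamber as both descriptions require, so one arm may be treated contrary to the protocol.
- **Interpretation.** A difference in EPO, ROS or cytokines could be reported as an oxygen effect against a sham wrongly described as matched. This cannot be repaired once patients have been treated.

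**Working it through.** **1. The settings side by side**

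| Parameter | Sections 2.5 and 2.6 | Active arm (2.6.1) | Sham (2.6.2) |
|---|---|---|---|
| Oxygen | 32–40% vs about 21% | 32–40% | about 21% |
| Pressure | identical (named) | 1500 hPa | about 1000 hPa |
| CO2 | identical (covered by the general phrase) | 0.7–1.9% | about 0.03% |
| Hydrogen | identical (covered by the general phrase) | 0.5–1% | about 0.00005% |

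Pressure is named in both places with incompatible content. CO2 and hydrogen conflict through the statement that every other environmental parameter is the same.

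**2. The plan's own ratio.** Section 2.6.1 says hydrogen is 10,000 to 20,000 times the atmospheric level. From the stated fractions, 0.5 / 0.00005 = 10,000 and 1 / 0.00005 = 20,000. The figure is reproduced, so the active and sham hydrogen settings are consistent with each other and do not look like a slip in one number.

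**3. Size of the differences if Sections 2.6.1 and 2.6.2 govern.** Partial pressure = fraction × chamber pressure.

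- Oxygen, active: 0.32 × 1500 = 480 hPa and 0.40 × 1500 = 600 hPa. Sham: 0.21 × 1000 = 210 hPa. Ratios: 480/210 = 2.3 and 600/210 = 2.9.
- CO2, active: 0.007 × 1500 = 10.5 hPa and 0.019 × 1500 = 28.5 hPa. Sham: 0.0003 × 1000 = 0.3 hPa. Ratios: 35 and 95.
- Hydrogen, active: 0.005 × 1500 = 7.5 hPa and 0.01 × 1500 = 15 hPa. Sham: 0.0000005 × 1000 = 0.0005 hPa. Ratios: 15,000 and 30,000.
- Chamber pressure above outside: 1500 − 1000 = 500 hPa in the active arm, and about 0 in the sham.

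**4. How much of the oxygen rise comes from pressure.** The rise is 480 − 210 = 270 hPa at 32% oxygen and 600 − 210 = 390 hPa at 40%. Fraction and pressure multiply, so the share depends on which is raised first.

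| Order | At 32% oxygen | At 40% oxygen |
|---|---|---|
| Pressure first (0.21 × 1500 = 315, a gain of 105) | 105/270 = 39% | 105/390 = 27% |
| Fraction first (320 or 400 hPa at 1000 hPa) | (480 − 320)/270 = 59% | (600 − 400)/390 = 51% |

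Pressure therefore accounts for 27–59% of the rise. With pressure equal at 1000 hPa, as Section 2.6 implies if the sham stays at room pressure, the same oxygen fractions would give only 320–400 hPa, or 1.5–1.9 times the sham.

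**The case against.** The pressure conflict cannot be argued away. The case on the other side concerns its weight.

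- **The arm-specific sections probably govern.** They give numbers for four parameters in each arm, while Section 2.6 has one general sentence. This is a strong inference, but the article does not say so, and the sentence it would overrule is explicit about pressure.
- **The objectives in Section 1 ask about NBO, not oxygen fraction.** Section 2.6.1 can be read as defining NBO by all its settings, so the randomised comparison answers a legitimate question. This stands: only attribution to oxygen is lost, and the mechanistic text is mostly hedged. But Section 1 also defines NBO as a higher oxygen fraction at atmospheric pressure, so the oxygen reading comes from the protocol itself.
- **Section 2.5 is softer than Section 2.6.** It speaks of similar conditions, not identical ones. That is so, but a gap of 500 hPa is not similar either.
- **The decompression period is an argument from silence.** Section 2.6.2 lists no session phases, and Section 2.6 says duration is the same. This stands, and the conclusion does not rest on it.
- **The blind has other safeguards:** chambers identical in appearance, concealed oxygen indicators, a standardised procedure, and operators kept out of data collection and analysis. This stands too. The documents do not show that patients would notice the difference.
- **Pressure acts partly by raising oxygen partial pressure,** so it is not wholly a rival explanation. That is correct. CO2 and hydrogen are the clearly non-oxygen differences.

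**Conclusion.** The concern holds. The two descriptions of the arms contradict each other, directly on pressure and by plain implication on CO2 and hydrogen.

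The consequence depends on which text is right, and the article does not settle that:

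- **If Section 2.6 governs,** only the oxygen fraction differs, and the error is confined to the settings listed in Sections 2.6.1 and 2.6.2.
- **If Sections 2.6.1 and 2.6.2 govern,** four parameters differ instead of one, by the amounts worked out above. Randomisation still supports a valid estimate of the combined exposure against room air. The sham lacks the property claimed for it in Sections 2.5 and 2.6, and outcome differences cannot be credited to oxygen concentration. The sentence that rests the blind on similar environmental conditions would be untrue as written, which is not the same as showing that the blind would fail.

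The sizes take the approximate sham values at face value and assume the active settings hold across their stated ranges. The contradiction itself needs no assumption. It must be fixed before treatment starts, because it leaves the tested intervention undefined.

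**What to change.** Before first enrolment, which Section 3 schedules for March 2026, add one table of chamber settings per arm (oxygen, pressure, CO2, hydrogen and session phases) and make Sections 2.5, 2.6, 2.6.1 and 2.6.2 agree with it. The sponsor must say which settings are right.

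**Route A: the arm-specific settings are right.**
- In Section 2.6, withdraw the claim that pressure and ambient conditions are the same in both arms.
- In Section 2.5, say that the placebo omits more than the oxygen adjustment, and state what the blind rests on now that environmental conditions are not similar.
- In the objectives (end of Section 1) and in Section 5, define the intervention as the combined chamber exposure and drop attribution to oxygen specifically.

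This costs wording only, with no added patients or procedures. The price is a narrower conclusion.

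**Route B: Section 2.6 is right.** Correct Sections 2.6.1 and 2.6.2 so that pressure, CO2 and hydrogen match between arms and only oxygen differs. This also needs no extra patients. If the chamber is now planned to run at the listed settings, the operating settings of at least one arm must change.

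### Section 2.6 calls all conditions except oxygen concentration identical between arms, but 2.6.1 and 2.6.2 set different pressure, carbon dioxide and hydrogen

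*Protocol article*

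**What the plan says.** Section 2.6 (Intervention Planned) describes both arms as treated in the same chamber. The active arm receives 32–40% oxygen, while "for the placebo group, the oxygen level will be set to approximately 21% (room air". It then states: "All other environmental parameters—such as chamber pressure, duration of sessions, and ambient conditions—will be identical between the two groups". The double-blind statement follows directly.

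Section 2.6.1 sets the active arm's conditions, "including oxygen levels of 32–40% (compared with about 21% in the atmosphere), pressure maintained at 1500 hPa (compared with about 1000 hPa outside", and continues with "carbon dioxide levels between 0.7 and 1.9% (compared with 0.03% in the atmosphere), and hydrogen levels between 0.5 and 1" (per cent). It also allows 10 minutes at the end of each session for finalization and decompression.

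Section 2.6.2 sets the sham: "Patients will be exposed to atmospheric conditions in the same NBO chamber", "including oxygen levels at about 21%, pressure maintained at about 1000 hPa", "carbon dioxide levels at about 0.03%, and hydrogen levels at about 0.00005" (per cent). It says the comparator separates the effects of the active treatment "from the natural course of treatment without enhanced oxygen exposure".

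Two other places bear on the point. Section 2.5 (Randomization and Blinding) describes placebo sessions as imitating the active ones apart from the oxygen adjustment, and lists similar environmental conditions among the means of concealing assignment. The Introduction defines normobaric therapy as oxygen given at atmospheric pressure, and describes hyperbaric therapy as typically at 1.4 ATA or more.

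**The concern.** The sentence in 2.6 names chamber pressure as equal, and the next two subsections give it two different values. Carbon dioxide and hydrogen, which fall under its ambient conditions, also differ between the arms. Nothing elsewhere in the article reconciles the statements.

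Two things are at stake. First, the sentence defines the contrast that every between-group comparison tests. Someone relying on 2.6 would take a difference in erythropoietin, or in any other outcome, as an effect of oxygen concentration. Under the arm-specific settings, oxygen fraction, pressure, carbon dioxide and hydrogen all change together, and a two-arm trial cannot separate them. Second, the sentence leads into the claim of double blinding, so part of the stated support for the blind is an equality that the protocol's own settings deny.

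**Working it through.** **Inputs, as printed**

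| Parameter | Active (2.6.1) | Sham (2.6.2) | Overview (2.6) |
|---|---|---|---|
| Oxygen | 32–40% | about 21% | 32–40% vs about 21% |
| Pressure | 1500 hPa | about 1000 hPa | identical |
| Carbon dioxide | 0.7–1.9% | about 0.03% | identical (ambient conditions) |
| Hydrogen | 0.5–1% | about 0.00005% | identical (ambient conditions) |

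The oxygen row agrees in all three places. The other three rows do not.

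**The plan's own ratio.** Section 2.6.1 gives hydrogen as 10,000 to 20,000 times the atmospheric level. Check: 0.5 / 0.00005 = 10,000 and 1 / 0.00005 = 20,000. It reproduces, so the printed settings are internally coherent.

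**Partial pressure = gas fraction × total pressure** (dry gas).

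Oxygen:
- Active: 0.32 × 1500 = 480 hPa; 0.40 × 1500 = 600 hPa.
- Sham: 0.21 × 1000 = 210 hPa.
- Ratio: 480 / 210 = 2.29; 600 / 210 = 2.86.
- Difference: 480 − 210 = 270 hPa; 600 − 210 = 390 hPa.
- Fraction alone: 0.32 / 0.21 = 1.52; 0.40 / 0.21 = 1.90.

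Carbon dioxide:
- Active: 0.007 × 1500 = 10.5 hPa; 0.019 × 1500 = 28.5 hPa.
- Sham: 0.0003 × 1000 = 0.3 hPa.
- Ratio: 35 to 95.

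Hydrogen:
- Active: 0.005 × 1500 = 7.5 hPa; 0.01 × 1500 = 15 hPa.
- Sham: 0.0000005 × 1000 = 0.0005 hPa.
- Ratio: 15,000 to 30,000.

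**If pressure really were identical.** Section 2.6 gives no shared value, so both printed pressures are tried. The oxygen ratio is 1.52–1.90 in either case, but the difference depends on the pressure.
- Both at 1000 hPa: 320 − 210 = 110 and 400 − 210 = 190 hPa, which is 110 / 270 = 41% and 190 / 390 = 49% of the difference under the arm-specific settings.
- Both at 1500 hPa: the sham has 0.21 × 1500 = 315 hPa; 480 − 315 = 165 and 600 − 315 = 285 hPa, which is 165 / 270 = 61% and 285 / 390 = 73%.

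**Which statement is more likely wrong.** Three features favour the arm-specific settings. They are explicit numbers for all four parameters. The active arm's pressure is set against a lower outside pressure and comes with a decompression period. The sham is called atmospheric and given its own pressure. Against them stands the Introduction: 1500 hPa is 1500 / 1000 = 1.5 times the outside pressure that 2.6.1 prints, or about 1.48 atm if 1 atm is 1013.25 hPa. That is not atmospheric pressure, and it exceeds the 1.4 ATA that the Introduction associates with hyperbaric treatment.

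**The case against.** The strongest reply is that the documents do not prove which statement is wrong. By the Introduction's definition, 1500 hPa could itself be the misfit and 2.6 the intended design. The room-air remark in 2.6 does not settle it, because it describes the oxygen level and says nothing about pressure. This stands in part. The detailed settings remain the better reading, but the sponsor has to confirm them, and the sentence in 2.6 cannot be declared the only possible error.

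A second reply is that 2.6.1 already presents the active treatment as a bundle, and that nothing in the article commits the sponsor to crediting oxygen fraction alone. That is fair. However, 2.5, 2.6 and the end of 2.6.2 all frame the contrast around oxygen, and the sentence in 2.6 denies the other differences outright.

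Some stronger readings are tempting and should not be adopted:
- **Section 2.5 makes the same false claim.** It says similar, not identical, and mainly describes how the chambers look and are set up. It needs aligning, but it is weaker evidence.
- **The blind will fail.** The article describes decompression only for the active arm, which is a possible cue. It gives no evidence that patients or staff would detect it.
- **Sham patients may be pressurised by mistake and receive 315 hPa of oxygen.** Section 2.6.2 prints an explicit sham pressure, and nothing suggests that operators would work from the overview paragraph.
- **Section 2.6 understates the oxygen difference by about half.** The 41–49% figure assumes a shared 1000 hPa. A shared 1500 hPa gives 61–73%, and 2.6 specifies neither.

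**Conclusion.** The contradiction is real and lies in the current text: the equality stated in 2.6 cannot hold together with the settings in 2.6.1 and 2.6.2. Under the arm-specific settings the oxygen contrast is about 480–600 against 210 hPa, 2.29–2.86-fold, compared with 1.52–1.90-fold for fraction alone. Pressure, carbon dioxide and hydrogen also differ. A between-group difference can therefore be credited to the combined chamber exposure and to nothing narrower.

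This rests on the arm-specific settings being the intended ones, on the approximate sham values (about 21%, about 1000 hPa), and on ignoring water vapour. The last two affect only the precision of the hPa figures. The inconsistency itself needs none of these assumptions. No direction or size of effect on any outcome is assumed. The text should be corrected before enrolment, but the point does not by itself invalidate the comparison of the two arms as randomized.

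**What to change.** 1. Have the sponsor confirm the settings in 2.6.1 and 2.6.2, given the Introduction's definition.
2. If they are confirmed, replace the whole sentence in 2.6, not only its mention of pressure. For example: session duration and chamber appearance are the same in both groups; pressure, oxygen, carbon dioxide and hydrogen differ as given in 2.6.1 and 2.6.2.
3. In 2.6, describe the tested contrast as the combined chamber exposure (about 480–600 against 210 hPa oxygen, with the pressure, carbon dioxide and hydrogen differences), and do not attribute effects to oxygen concentration alone.
4. In 2.5, limit the reference to environmental conditions to what is actually matched. Acknowledge that pressurisation with decompression, described only for the active arm, may be a cue to allocation.

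This changes text only; arm settings, patients and visits stay as they are. Section 3 schedules the first participant for March 2026, so the correction can precede enrolment. The real cost is to the blinding argument. It can no longer cite identical pressure or ambient conditions, and has to rest on chamber appearance and setup, session duration and concealed oxygen indicators. Whether to add a safeguard is for the sponsor to decide.

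The alternative is to make 2.6 true by matching pressure, carbon dioxide and hydrogen in the sham. That would isolate oxygen fraction and remove the pressure cue, but it redesigns the arm. At 1500 hPa and 21% oxygen the sham would receive 315 hPa, 1.5 times the 210 hPa of room air, and would no longer be the comparator that 2.6.2 describes.
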